## 2 Study objectives

In this trial we will test the hypothesis that supplementation with IHAT eliminates iron deficiency and improves haemoglobin levels in young children without increasing infectious diarrhoea or promoting negative changes in the gut microbiome or inducing gut inflammation.

### There are four null hypotheses in the study:

1) non-inferiority of IHAT compared to ferrous sulphate for efficacy (in terms of Hb and iron deficiency correction: i.e. IDA) response probability (or prevalence). In this case we are testing the null hypothesis that: response probability in the IHAT arm minus the response probability in the ferrous sulphate arm is less than or equal to  $-0.1$ . **We define 'response' for IDA as correction of iron deficiency and either achieving a normal Hb or an increase of at least 1 g/dL after 12 weeks of iron supplementation.**

2) superiority of IHAT compared to ferrous sulphate in terms of incidence density of diarrhoea. Here the null hypothesis is that the mean number of new episodes in the IHAT arm is greater than or equal to the mean number in the  $\text{FeSO}_4$  arm.

3) superiority of IHAT compared to ferrous sulphate in terms of prevalence of diarrhoea. Here the null hypothesis is that the prevalence of diarrhoea in the IHAT arm is greater than or equal to the prevalence in the  $\text{FeSO}_4$  arm.

4) non-inferiority of IHAT compared to placebo in terms of prevalence of diarrhoea. Here the null hypothesis is that the prevalence of diarrhoea in the placebo arm minus the prevalence in the IHAT arm is less than or equal to  $-0.1$ .

**The primary objective for this trial is to show non-inferiority of IHAT in relation to ferrous sulphate at correcting IDA, and in terms of diarrhoea to show superiority in relation to ferrous sulphate and non-inferiority in relation to placebo (as defined above).** Secondary objectives are to show that IHAT is non-detrimental with respect to enteric pathogen burden, the gut microbiome, and intestinal inflammation.

## 2.1 Study endpoints

### Primary endpoints:

There are 4 primary endpoints of the trial:

1. iron deficiency at 12 weeks
2. haemoglobin levels at 12 weeks
3. 'incidence density' of moderate-severe diarrhoea over the 12 weeks (i.e. the number of new moderate-severe diarrhoea episodes per child over the 12 weeks intervention)
4. 'period prevalence' of moderate-severe diarrhoea over the 12 weeks intervention period (i.e. the proportion of children with at least one episode of moderate-severe diarrhoea over the 12 weeks intervention)

### Efficacy primary endpoints:

To assess iron deficiency we will take into consideration the most up-to-date recommendation from WHO who are currently conducting a consultation on this matter. The new WHO guidelines will include a recommendation for the best marker of iron deficiency in the context of inflammation and we expect this to be either using ferritin alone or the sTfR/logferritin index, where in both cases ferritin values will be inflammation-adjusted. There are several models we can use to adjust ferritin for inflammation, for example use unadjusted ferritin with the cut-off with optimal sensitivity and specificity from the Malawi study ( $<18 \mu\text{g/L}$ ), use the CRP/AGP regression model being investigated by [name] (BRINDA) to adjust ferritin values, use the Thurnham et al (38) stratified adjustment or the continuous adjustment used by Engle-Stone et al (39). The choice of the method for adjusting ferritin concentrations and of which marker to use to define ID (ferritin alone or the sTfR/logferritin index) will be made at the time of locking the data analysis plan, in consultation with an expert on this matter ([name]), our BMGF Program Officer ([name]) and taking into consideration the results from Brinda and the results from the ongoing WHO consultation on this matter.

Iron deficiency and haemoglobin levels at 12 weeks will be used to define the prevalence of IDA which we will use to assess non-inferiority of IHAT relative to  $\text{FeSO}_4$  in terms of efficacy. **We will determine the proportion of children who resolve iron deficiency and either achieve a**

**normal Hb or an increase in Hb of at least 1 g/dL after 12 weeks of iron supplementation.**

**Safety primary endpoints:**

**Incidence density and period prevalence of moderate-severe diarrhoea will be used to show superiority of IHAT in relation to ferrous sulphate and non-inferiority of IHAT in relation to placebo.**

Diarrhoea is defined as 3 or more loose or watery stools per day and **moderate-severe diarrhoea** refers to those diarrhoea episodes where (i) the child passes more than 5 loose or watery stools per day, (ii) there is blood in the stool (dysentery), or (iii) the child shows signs of clinical dehydration (assessed by the study nurse based on physical signs such as little or no urination, sunken eyes, and skin that lacks its normal elasticity). These episodes will require treatment (including ORS) and will be recorded as adverse-events.

**'Incidence density' is defined as the number of new moderate-severe diarrhoea episodes per child over the 12 weeks intervention and 'period prevalence' is defined as the proportion of children with at least one episode of moderate-severe diarrhoea over the 12 weeks intervention.**

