**Secondary endpoints:**

Secondary endpoints will be faecal microbiome diversity and profile (particularly in terms of abundance of Enterobacteria), abundance of enteric pathogens, faecal calprotectin (marker of gut inflammation), hospitalisation and morbidity (data collected three times per week using the questionnaire developed in the HIGH study), malaria infection, treatment failures (i.e. the number of children who have to discontinue the study intervention because their Hb falls below 7 g/dL), the proportion of days a child has diarrhoea over the 12 weeks intervention period ('longitudinal prevalence' of diarrhoea), the proportion of days a child has moderate-severe diarrhoea over the 12 weeks period ('longitudinal prevalence' of moderate-severe diarrhoea), 'incidence density' of bloody diarrhoea (i.e. the number of bloody diarrhoea episodes per child-month of observation), markers of systemic inflammation (serum CRP and AGP), and systemic markers of iron handling (hepcidin, sTfR, transferrin saturation and circulating non-transferrin bound iron - NTBI).

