## **7 Discontinuation criteria**

## **7.1 Participant's premature termination**

Mothers/guardians of participating children have the right to stop their children's participation in the study at any time without giving a reason and this will not affect the medical care that would normally be received. The trial team may also withdraw a participant from the study if deemed necessary at any time taking in to consideration the reasons mentioned below. The reason for a participant's premature termination will be documented on the appropriate page of the CRF and specified which of the following possible reasons were responsible for the premature termination:

- Serious Adverse Event
- Adverse Event
- Participant's consent withdrawal
- Development of withdrawal criterion
- Protocol deviation
- Migrated/moved from the study area
- Lost to follow-up

A 'lost to follow-up' is any participant who completed all protocol specific procedures up to the administration of the investigational product or intervention, but was then lost during the study period to any further follow-up, with no safety information and no efficacy endpoint data ever became available.

In case the participant decides to withdraw participation or consent during the study, we will not work on participant's samples without permission, but any information already generated from the samples will be kept and used. The study clinician may also ask for tests for the participant's safety. The PI will inquire about the reason for any withdrawal and follow-up with the participant regarding any unresolved AEs.

For withdrawn participants no specific data will be collected. Our sample size takes into account a dropout rate of 15% but this will be monitored closely and if the observed dropout rate increases above this level we will replace subjects to ensure we reach our target sample size of n=600 completed.

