#### **There are four null hypotheses in the study:**

- 1) non-inferiority of IHAT compared to ferrous sulphate for efficacy (in terms of Hb and iron deficiency correction: i.e. IDA) response probability (or prevalence). In this case we are testing the null hypothesis that: response in the IHAT arm minus the response probability in the ferrous sulphate arm is less than or equal to  $-0.1$ . We define 'response' for IDA as correction of iron deficiency and either achieving a normal Hb or an increase of at least 1 g/dL after 12 weeks of iron supplementation.
- 2) superiority of IHAT compared to ferrous sulphate in terms of incidence density of diarrhoea. Here the null hypothesis is that the mean number of new episodes in the IHAT arm is greater than or equal to the mean number in the FeSO4 arm.
- 3) superiority of IHAT compared to ferrous sulphate in terms of prevalence of diarrhoea. Here the null hypothesis is that the prevalence of diarrhoea in the IHAT arm is greater than or equal to the prevalence in the FeSO4 arm.
- 4) non-inferiority of IHAT compared to placebo in terms of prevalence of diarrhoea. Here the null hypothesis is that the prevalence of diarrhoea in the placebo arm minus the prevalence in the IHAT arm is less than or equal to  $-0.1$ .

Because this is a pilot study we do not formally adjust for multiple testing due to the four hypotheses. This is because any significant results will be tested again in a pivotal study.

The trial is powered to show non-inferiority of IHAT relative to ferrous sulphate for the 12 weeks efficacy response probability. At the 12 weeks time-point (i.e. Day 85), the estimated odds ratio between the IHAT and FeSO4 arms will be calculated, together with a 90% one-sided confidence interval. If the lower limit of the confidence interval for this difference is above 0.583 (equivalent to a 10% absolute difference if FeSO4 response rate is 0.3), then non-inferiority of IHAT in terms of efficacy will be declared.

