Because many trials conducted in Africa and other developing countries with the gold standard ferrous sulphate or ferrous fumarate supplementation still fail to provide anaemia resolution in interventions shorter than 6 months, we have considered here that an increase of 1 g/dl in Hb after 3 months is an indication of efficacy, even though we accept that this is not clinical efficacy. We have based our assay sensitivity from data published with relevant iron supplement studies in children available in the literature (3, 7, 52). We plan, however, to use the data collected in the proposed study to conduct an exploratory analysis to test for assay sensitivity. These data will be very useful so that adequate treatment effect sizes can be used to power any future studies, in particular a pivotal trial, both for ferrous sulphate and IHAT supplementation effects.

Due to this trial being a pilot study, any significant results will be re-tested in the pivotal 'full' trial (BMGF full award). Thus, we considered a larger than traditional type-I error rate of 10%. Assuming that 30% (i.e. a response probability of 0.3) of the children in both arms will resolve iron deficiency and either achieve a normal Hb or an increase of at least 1 g/dL after 12 weeks of iron supplementation (3, 7, 52), then a sample size of 200 in the IHAT arm and 200 in the ferrous sulphate arm will provide 89% power to show non-inferiority with a non-inferiority margin of 0.1 (0.583 on the odds-ratio scale). In other words, the trial will have 89% power (at a 10% one-sided significance level) to show that the lower boundary of the confidence interval of the odds ratio between IHAT and ferrous sulphate is more than 0.583 at 12 weeks.

We have based our calculation above on assay sensitivity data taken from other studies with iron supplements reported in the literature, but we will also perform an exploratory analysis to test for assay sensitivity, and this information will be used to power the potential future pivotal study.

We have considered two options for modelling the diarrhoea outcome: 1) 'period prevalence', i.e. the proportion of children with at least one episode of moderate-severe diarrhoea over the 12 weeks intervention period; 2) 'incidence density'. i.e. the number of new diarrhoea episodes per child over the 12 weeks intervention period. The modelling of how the power of the trial varies according to assumptions for each of these outcomes is detailed below.

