## 8.2 Statistical analysis

The data analysis plan will be fully developed prior to database lock and will be done with the expert input from [name] of the MRC Biostatistics Unit in Cambridge. Briefly, for the primary analysis, we will fit a logistic regression to the efficacy outcome data, adjusting for the strata created by age and Hb level groups prior to enrolment. The odds ratio for effect of IHAT relative to ferrous sulphate will be estimated, and if the lower 90% one-sided confidence interval is above 0.583 (equivalent to the 10% non-inferiority margin above), non-inferiority will be declared for IHAT. The diarrhoea endpoint will be analysed in a similar way, but tested for superiority (i.e. if the one-sided p-value for the Wald test of the effect of IHAT is less than 0.1) for the comparison between IHAT and ferrous sulphate. For the primary non-inferiority hypothesis we will conduct per-protocol and intention-to-treat analyses and for the superiority hypotheses we will conduct intention-to-treat analyses.

The secondary endpoints (calprotectin, NTBI etc) will be tested using linear regression with the same covariates. Morbidity data will be analysed using multiple regression analysis controlling for possible confounders.

In relation to the microbiome data analysis we will work together with our collaborators in the Sanger Institute and use the most up to date bioinformatics methodology available at the time of data analysis to investigate the impact of treatment arm and time in the composition of the gut microbiome. Since this analysis will only occur in late 2018/early 2019, it is premature to decide the strategy for data analysis now as this is a fast moving field with new and better bioinformatics tools becoming available every couple of months. The Sanger Institute works very closely with the European Bioinformatics Institute (EBI) (housed in the same campus) to ensure they use the very latest tools in their microbiome analysis.

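### The primary incidence density (H2) has no time at risk, so unequal withdrawal could bias the IHAT versus ferrous sulphate rate ratio in either direction

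*Supplement*

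**What the plan says.** Protocol section 2.1 (safety primary endpoints) fixes the primary measure: incidence density "is defined as the number of new moderate-severe diarrhoea episodes per child over the 12 weeks intervention". The protocol summary, section 5.2 and section 8.1 use the same denominator. Hypothesis 2 (sections 2 and 8.1) has as its null that "the mean number of new episodes in the IHAT arm is greater than or equal to the mean number" in the ferrous sulphate arm.

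In the secondary endpoints of section 2.1, incidence density of bloody diarrhoea means "the number of bloody diarrhoea episodes per child-month of observation". One term therefore has two denominators, and only the secondary one uses time under observation.

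On incomplete follow-up, section 7.1 says "Our sample size takes into account a dropout rate of 15" per cent, and that no specific data will be collected for withdrawn participants. Section 8.1 gives the same 15% as overall non-completion, without a split by arm. Children who stop treatment because Hb falls below 7 g/dL stay under follow-up (sections 4.3 and 5.1.3).

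On analysis, section 8.2 describes a logistic regression for efficacy and then says: "The diarrhoea endpoint will be analysed in a similar way, but tested for superiority". Superiority is claimed "if the one-sided p-value for the Wald test of the effect of IHAT is less than 0.1", by intention to treat. The section names no count model, no exposure offset and no rule for a child observed for part of the 12 weeks. It leaves detail to a data analysis plan that is not among the documents.

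**The concern.** An episode count rises with the time a child is watched. A child who leaves in week 3 can contribute at most three weeks of episodes. If that child enters the arm mean with the same weight as a child watched for 12 weeks, the mean depends on how long the arm was observed as well as on how often its children had diarrhoea. The plan expects about one child in seven not to complete, so partial follow-up is foreseeable.

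What is at stake is one of the trial's two superiority claims over ferrous sulphate. More or earlier withdrawal on IHAT would make IHAT look better than it is. More or earlier withdrawal on ferrous sulphate would hide part of a real advantage.

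**Working it through.** **Inputs from the protocol.** 1.28 episodes per child over 84 days (8.1); 36% of children with at least one episode in the same cited Gambian study (8.1); planned rate ratio 0.8 (8.1); one-sided 10% test (8.1, 8.2); 200 per arm in the power calculation (8.1) and 235 per arm randomised (3.1); 15% overall non-completion (7.1, 8.1).

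**Assumptions, not in the documents.** Withdrawal by arm as shown in the table; withdrawal times uniform over the 12 weeks and unrelated to diarrhoea risk; withdrawn children kept with their observed counts.

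**The plan's own figure.** Section 8.1 states almost 90% power at a ratio of 0.8. Take Poisson counts, 200 per arm, full exposure for every child, and variance at 1.28 in both arms. SE(log ratio) = √(2/(200 × 1.28)) = 0.0884, and power = Φ(0.2231/0.0884 − 1.2816) = 89.3%. With 1.28 as the mean of the two arms it is 89.0%; with 1.28 as the ferrous sulphate rate, 86.4%. The stated figure is thus reproduced with every child observed for the full 12 weeks.

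**Dispersion.** A Poisson mean of 1.28 would leave 1 − e^(−1.28) = 72% of children with an episode, not 36%. A negative binomial that matches both figures solves (1 + 1.28/k)^(−k) = 0.64, giving k = 0.243.

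**Bias in the ratio.** With a fraction d withdrawing at uniform times, mean exposure is 1 − d/2. With equal true rates the apparent ratio is (1 − d_IHAT/2)/(1 − d_FeSO4/2):
- 15%/15%: 0.925/0.925 = 1. No bias in the ratio, although both means are 7.5% too low.
- 20%/10%: 0.90/0.95 = 0.947.
- 25%/5%: 0.875/0.975 = 0.897.
- 10%/20%: 0.95/0.90 = 1.056.

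**Type I error, normal approximation, 20%/10%.** SE = √[(1/(1.28 × 0.90) + 1/0.243 + 1/(1.28 × 0.95) + 1/0.243)/235] = 0.205. Then Φ(0.054/0.205 − 1.2816) = 15.4%.

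**Simulation** (20,000 trials per row, 235 per arm, no true effect, robust Wald test, nominal 10%):

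| Withdrawal IHAT / FeSO4 | Per child, k = 0.243 | Per child-time, k = 0.243 | Per child, Poisson | Per child-time, Poisson |
|---|---|---|---|---|
| 15% / 15% | 10.5% | 10.6% | 10.0% | 10.0% |
| 20% / 10% | 15.9% | 10.5% | 25.9% | 10.2% |
| 25% / 5% | 23.1% | 10.5% | 49.0% | 10.1% |
| 10% / 20% | 6.5% | 10.7% | 2.7% | 10.1% |

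**Loss of a true benefit.** With a true ratio of 0.8 and withdrawal of 10%/20%, the per-child ratio moves to 0.8 × 1.056 = 0.844. Power is 32% per child against 42% per child-time with k = 0.243, and 71% against 89% with Poisson counts.

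**The case against.** The strongest reply is that the protocol sets the target, mean episodes over 12 weeks, while the estimator belongs to the later analysis plan. A 12-week mean can be estimated with a log-time offset, and section 8.1 already speaks of a rate ratio. That reply carries weight for the missing model. It carries less for the denominator: the protocol itself fixes episodes per child, uses child-months for the sister endpoint, and, unlike for the iron-deficiency marker in section 2.1, does not say that the choice is deferred.

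Second, no section states that an early leaver is counted as a full child. Intention to treat leans that way, but section 7.1 also speaks of replacing dropouts to reach 600 completers. If only fully observed children were analysed, exposure would be equal and this mechanism would vanish, with selection as a different worry. This stands, and the point is therefore conditional.

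Third, the splits by arm are assumptions. Blinded, colour-matched products, daily supervised dosing, no withdrawal criterion for diarrhoea, continued follow-up below 7 g/dL, and the monitoring board's review of drop-out rates (section 6) all work against a large gap. This stands too.

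A reader might infer that the definition favours IHAT and makes false superiority likely. The documents do not support that. Section 1.4 expects better compliance on IHAT; if this meant fewer IHAT withdrawals, the test would be conservative. A reader might also infer that hypotheses 3 and 4 are flawed in the same way. A crude 12-week proportion is a conventional period prevalence, and no size has been worked out for them.

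**Conclusion.** The point holds in conditional form. The primary incidence density has no time at risk, in a plan that expects 15% non-completion and collects no specific data on withdrawn children. If withdrawn children stay in with their observed counts, equal withdrawal does no harm to the ratio and unequal withdrawal biases it in either direction. At an assumed 20%/10% split, the artefact of 0.947 is a 5.3% apparent reduction, about a quarter of the planned 20%, and one-sided type I error is about 16% rather than 10%. At 10%/20% it is about 6.5%, with lost power.

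These sizes rest on the assumed splits, on uniform withdrawal unrelated to diarrhoea, and on k = 0.243. That value combines two figures which the protocol does not say were ascertained in the same way; less dispersion makes the distortion larger, as the Poisson columns show. Neither an actual imbalance nor its direction can be read from the documents.

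**What to change.** In sections 2.1, 8.1 (hypothesis 2) and 8.2:
- Define the primary incidence density as new moderate-severe episodes per child-time under diarrhoea surveillance from Day 1 to Day 85, in line with the bloody-diarrhoea endpoint.
- Estimate the IHAT to ferrous sulphate rate ratio with a count model that allows for overdispersion (negative binomial, or Poisson with robust errors), with log(days observed) as offset and the age and Hb stratification factors as covariates.
- State that withdrawn children enter with their observed counts and days, and report days observed and withdrawals by arm.
- State that the offset corrects only for withdrawal unrelated to diarrhoea risk, and add a sensitivity analysis for withdrawal that is related to it.

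For hypotheses 3 and 4, a 12-week risk from time to first episode, censored at last observation, is an optional sensitivity analysis and not a correction.

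The cost is wording in the protocol and the analysis plan. The daily visits (5.1.3) and the three-times-weekly morbidity questionnaire (5.2.1) already supply the days observed.

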**Secondary endpoints:**

Secondary endpoints will be faecal microbiome diversity and profile (particularly in terms of abundance of Enterobacteria), abundance of enteric pathogens, faecal calprotectin (marker of gut inflammation), hospitalisation and morbidity (data collected three times per week using the questionnaire developed in the HIGH study), malaria infection, treatment failures (i.e. the number of children who have to discontinue the study intervention because their Hb falls below 7 g/dL), the proportion of days a child has diarrhoea over the 12 weeks intervention period ('longitudinal prevalence' of diarrhoea), the proportion of days a child has moderate-severe diarrhoea over the 12 weeks period ('longitudinal prevalence' of moderate-severe diarrhoea), 'incidence density' of bloody diarrhoea (i.e. the number of bloody diarrhoea episodes per child-month of observation), markers of systemic inflammation (serum CRP and AGP), and systemic markers of iron handling (hepcidin, sTfR, transferrin saturation and circulating non-transferrin bound iron - NTBI).

